### 3.5. Adverse Events Assessment

Regarding patient safety, any adverse event related to the acupuncture treatment will be observed and reported by patients, practitioners or care providers during each patient visit. Although the participants in the study will not need medical assistance in the acupuncture treatments, which will occur during hemodialysis sessions, they will be under permanent medical surveillance. If any adverse reaction occurs during the intervention, emergency measures will be taken as appropriate.

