### 2.5. Blinding

The participants, the outcome assessor, the statistician and the Traditional Chinese Medicine practitioner will be blind to the allocation. Regarding the intervention itself, due to its specific nature, only the Traditional Chinese Medicine practitioner will not be blind to the verum acupuncture, sham and non-acupuncture groups.

To assess the effectiveness of the blinding, after the treatment, a questionnaire will be administered to ask the participants in the VA and SA groups what sort of acupuncture treatment (verum or sham) they believe they received. This question will allow the calculation of the James Blinding Index (BI) [21,22].

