### 3.6. Quality Control and Data Collection

Before the clinical trial begins, the research team will receive specialized training to ensure the quality of the study is maintained. Topics concerning the research process, eligibility criteria, data collection and management and assessment of adverse events will be covered.

Screening for eligibility, demographic and clinical-data collection and physical examinations will be performed by the TECSAM clinical team, acting as an independent assessor. The main researcher, the practitioner who will provide the acupuncture treatments, will not have access to patient data until anonymization, randomization and allocation procedures are complete. Baseline, after-treatment and follow-up outcome variables will be assessed by the TECSAM head nurse, who will not know to which group each subject is assigned. Moreover, the statistician will be unaware of the allocation details during the research period, to ensure that the objectivity and impartiality of the data are guaranteed.

The clinical trial will be stopped in case of serious adverse events. Participants will be withdrawn from the study if they are reluctant to continue or if they ask to be excluded.

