Many pharmacological interventions for people with CKD have known risks of adverse events and, according to the literature, acupuncture is commonly used in symptom management for chronic diseases as well as in palliative care [42]. However, the safety and efficacy of acupuncture for people with CKD remains largely unknown. Considering the aims of our study, we expect that verum acupuncture compared to sham acupuncture and non-acupuncture will improve the functional capacity of hemodialysis patients, as evidenced by an increase in the distance walked on the 6MWT and an increase in scores for quality of life. In addition, we expect an increase in handgrip strength and an improvement in peripheral muscle strength. According to Kim et al. (2016), there was low-quality evidence of the short-term effects of manual acupressure as an adjuvant intervention for fatigue, depression, sleep disturbance and uremic pruritus in patients undergoing regular hemodialysis [19]. Under this assumption, this study protocol was designed to check the effect of acupuncture after treatment and at 12 weeks post-treatment. In this way, we expect that the effect of acupuncture will be maintained in the follow-up period.

Some studies, especially in the pain field, suggest that three treatments per week obtain better results than one treatment per week [43,44]. We also expect to see better results with more intensive interventions compared to less frequent and prolonged interventions.

Following review of the literature and to the best of the authors’ knowledge, there are currently no comparable studies. Therefore, our trial seems to be an innovative study for exploring the effect of acupuncture and the frequency of treatment on improving FC and HRQOL in patients undergoing HD. Furthermore, supported by only a few clinical cases reported (personal data) prior to the design and development of the research project, it is possible to predict efficacy and the advantages of integrating acupuncture treatments into routine hemodialysis as a complementary therapy to conventional treatments.

Despite fulfilling strict methodological criteria, it is possible to identify limitations in our study protocol. First, the sample size; second, the TCM practitioner performing the acupuncture treatment will not be blinded due to the nature of the intervention; third, comorbidities inherent to chronic kidney disease may lead to a high dropout rate during the follow-up period.

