	(6b) Precise description of the control or comparator. If sham acupuncture or any other type of acupuncture-like control is used, provide details as for Items 1 to 3 above.	The placebo group (sham acupuncture) will receive a total of 9 acupuncture treatments, however, will be divided into subgroups A and B. Placebo subgroup A will receive three acupuncture sessions per week over 3 weeks and subgroup B will receive one a week for 9 weeks. Manual acupuncture will be performed as superficial needling (5 mm depth) at non-acupuncture points without an attempt to achieve a *De qi* sensation and without stimulation, lasting 25 min, using a sterilized stainless-steel needle (0.25 × 25 mm; Tewa, asia-med GmbH, [name]).The control group (waiting list) will not receive any acupuncture treatment during the study period. **List of Non-Acupuncture points used and their location** In the present study, the non-acupuncture points selected will be the points located on the non-meridian but near the acupuncture points described above. Non-Acupuncture point 1 (NA1) Located near KI3 (*Taixi*). On the posteromedial aspect of the ankle, at the midpoint of KI3 (*Taixi*) and (*Fuliu*). KI7 (*Fuliu*) is located on the posteromedial aspect of the leg, anterior to the calcaneal tendon, 2 *cun* superior to the prominence of the medial malleolus. Non-Acupuncture point 2 (NA2) Located near SP6 (*Sanyinjiao*). On the leg, at the midpoint of the medial side of the tibia, 1 *cun* distal from SP6 (*Sanyinjiao*). Non-Acupuncture point 3 (NA3) Located near ST36 (*Zusanli*). On the anterior aspect of the leg, at midpoint of ST37 (*Shangjuxu*) and the Gallbladder Meridian. ST37 (*Shangjuxu*) is located on the anterior aspect of the leg, on the line connecting ST35 with ST41, 6 *cun* inferior to ST35, on the tibialis anterior muscle. Non-Acupuncture point 4 (NA4) Located near HT7 (*Shenmen*). On the wrist, at the transverse crease of the wrist, at the midpoint of HT7 (*Shenmen*) and PC7 (Daling), between the Pericardium Meridian and the Heart Meridian. Non-Acupuncture point 5 (NA5) Located near CV4 (*Guanyuan*). On the lower abdomen, 1 *cun* lateral from CV6 (*Qihai*). CV6 (*Qihai*) is located 1.5 *cun* inferior to the center of the umbilicus, on the anterior median line.

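### Adverse event recording is tied to relatedness to acupuncture, so the waiting-list arm can contribute no events and the no-acupuncture safety comparison is lost

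*Protocol article*

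**What the plan says.** Section 3.5 of the protocol article sets the scope of safety recording: "any adverse event related to the acupuncture treatment will be observed and reported". The same sentence names the sources. Events are to be "reported by patients, practitioners or care providers during each patient visit". No sentence in the article provides for recording events regardless of cause, or for recording them in all three arms.

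Table 1, item 6b, describes the comparator: "The control group (waiting list) will not receive any acupuncture treatment during the study period".

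On who knows the allocation, Section 2.5 gives two statements. The first is "The participants, the outcome assessor, the statistician and the Traditional Chinese Medicine practitioner will be blind to the allocation". The next says that, for the intervention itself, "only the Traditional Chinese Medicine practitioner will not be blind to the verum acupuncture, sham and non-acupuncture groups". The limitations paragraph of the Discussion confirms that the practitioner is unblinded. Section 3.6 identifies this person's double role: "The main researcher, the practitioner who will provide the acupuncture treatments".

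Section 3.6 also has a stopping rule: "The clinical trial will be stopped in case of serious adverse events". It carries no relatedness condition. The Discussion states that "the safety and efficacy of acupuncture for people with CKD remains largely unknown".

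**The concern.** Cause is used as a filter before anything is written down. In a trial with a randomised no-acupuncture arm, this discards the safety information that the arm could give.

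Treatment is given during hemodialysis, to patients whom the Introduction and Discussion describe as having many physical problems and symptoms. When an event occurs in a session that combines dialysis and needling, its cause often cannot be settled case by case. A concurrent count in patients who are dialysed but not needled shows how many such events would have occurred anyway. Under the rule as worded, that count does not exist.

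The sham arm does not fully replace it. Sham patients are also needled, superficially and at other points, for the same nine sessions of 25 minutes. A harm common to both kinds of needling would appear in both arms and cancel in the verum-sham contrast.

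The filter also acts before any record exists. If attribution differs between verum and sham, the analysis can neither detect nor repair it.

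**Working it through.** The article states no safety figure to reproduce, so the check is mainly a reading of the sections together, with simple arithmetic for scale.

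**Group size (Section 3.4).** 20 per group with 15% dropout gives 20 / (1 − 0.15) = 23.5, rounded up to 24. This agrees with the article.

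**What the rule records.** Let p be the risk that a patient has any adverse event, and q the proportion of such patients whose event is called related to acupuncture. The expected number of patients recorded in an arm is 24 × p × q.

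- Waiting list: no acupuncture (Table 1, item 6b), so q = 0 and the count is 0 for every p.
- Verum and sham: if p is equal in the two arms, the ratio of expected counts is q(verum) / q(sham). It equals 1 only if attribution is the same in both.

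**What is lost in the control arm.** The values of p are assumptions, because the article gives none.

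| Assumed p | Expected controls with an event, 24p | Chance of none, (1 − p)^24 | Recorded under Section 3.5 |
|---|---|---|---|
| 10% | 2.4 | 8.0% | 0 |
| 20% | 4.8 | 0.5% | 0 |
| 30% | 7.2 | 0.02% | 0 |
| 50% | 12 | about 0 | 0 |

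An empty control column would therefore reflect the definition rather than the patients.

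**Who applies the filter.** Section 3.5 names three alternative sources: patients, practitioners and care providers. Section 2.5 lists participants as blind; the status of care providers is not stated; the practitioner is unblinded. Nobody is named as judging relatedness.

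**Recording against stopping.** Section 3.5 covers related events of any severity. Section 3.6 covers serious events of any cause. A serious event not thought related falls under the second and outside the first.

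**What full recording could deliver.** With 24 analysed per arm and the same p in both, the 95% half-width for a difference in proportions is 1.96 × √(2p(1 − p)/24):

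- p = 10%: 1.96 × √(0.18/24) = 17 percentage points
- p = 20%: 1.96 × √(0.32/24) = 23 points
- p = 50%: 1.96 × √(0.50/24) = 28 points

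A result of 0/24 against 5/24 only just reaches significance (two-sided Fisher p = 0.0496). For comparison, zero related events among 24 verum patients gives a one-sided 95% upper bound of 1 − 0.05^(1/24) = 11.7%.

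**Opportunity to collect.** Section 2.3 requires dialysis three times a week. Treatment of 3 or 9 weeks plus 12 weeks of follow-up is 15 or 21 weeks, so 3 × 15 = 45 to 3 × 21 = 63 scheduled contacts per patient.

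**The case against.** The strongest reply is that safety is neither one of the five objectives in the Introduction nor an outcome in Sections 3.1 and 3.2. The remark that safety is largely unknown is background in the Discussion. The text is also a condensed article: the word only is not in Section 3.5, adverse event forms and causality procedures usually sit in the full protocol, and Section 3.6 says that training will cover the assessment of adverse events. This limits the weight of the point but does not remove it. The article states a scope, and that scope is narrow. If the full protocol is wider, Section 3.5 misdescribes it. If it is not, no analysis plan can tabulate events that were never collected.

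Four stronger readings are tempting, and the document does not support them.

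- A reader might infer that an unblinded judgement decides what is counted. No judge of relatedness is named, and the practitioner is one of three sources, so a patient or nurse can report what the practitioner would not. Differential attribution is a possibility and has not been shown.
- A reader might infer that no rates can be compared between arms. Related events can occur and be reported in both needled arms, so verum against sham remains available.
- A reader might infer that the stopping rule has no data behind it. Section 3.5 places patients under permanent medical surveillance during the treatments, and the stopping rule has no relatedness condition. The two sections are mismatched, but nothing shows that serious events would be missed.
- A reader might infer from the 11.7% bound that the between-arm comparison is the only informative safety evidence. The bound is correct, but the comparison at 24 per arm is less precise. Its value lies in interpreting the verum count.

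**Conclusion.** The point holds in limited form. As worded, Section 3.5 makes the control count 0 of 24 by construction, and the trial gives up its no-acupuncture comparison for events that also occur in routine dialysis. Verum against sham survives for related events, but without a named blinded judge of relatedness and with an unblinded practitioner among the reporters. The set of events recorded and the set that triggers stopping differ and should be reconciled.

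This rests on the natural reading of Section 3.5 as the whole collection rule. The expected 2.4 to 12 unrecorded controls depend on assumed risks of 10% to 50% and show scale only. The two primary outcomes are unaffected. The change is still worth making before enrolment, because it is cheap and events not recorded at the time cannot be reliably reconstructed.

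**What to change.** Reword Section 3.5 so that:

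1. all adverse events are recorded in all three arms, with the same standard question at the same dialysis visits, from randomisation to the 12-week follow-up;
2. relatedness to acupuncture is assessed afterwards as a separate field, by someone blinded to group where feasible;
3. all events and related events are both tabulated by arm, as a descriptive comparison.

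Reconcile Section 3.5 with the stopping rule in Section 3.6 so that it is clear which events each covers; which clinical rule applies is for the investigators to decide. Reconcile the two sentences on the practitioner's blinding in Section 2.5 as well.

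The cost is a few more form entries at visits that already take place and one extra table. No visit, treatment or sample size changes. The remaining limitation is precision: with 24 per arm, only large differences would stand out.

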### 3.6. Quality Control and Data Collection

Before the clinical trial begins, the research team will receive specialized training to ensure the quality of the study is maintained. Topics concerning the research process, eligibility criteria, data collection and management and assessment of adverse events will be covered.

Screening for eligibility, demographic and clinical-data collection and physical examinations will be performed by the TECSAM clinical team, acting as an independent assessor. The main researcher, the practitioner who will provide the acupuncture treatments, will not have access to patient data until anonymization, randomization and allocation procedures are complete. Baseline, after-treatment and follow-up outcome variables will be assessed by the TECSAM head nurse, who will not know to which group each subject is assigned. Moreover, the statistician will be unaware of the allocation details during the research period, to ensure that the objectivity and impartiality of the data are guaranteed.

The clinical trial will be stopped in case of serious adverse events. Participants will be withdrawn from the study if they are reluctant to continue or if they ask to be excluded.

## 4. Discussion

The protocol described above refers to a parallel-group patient-assessor blinded randomized clinical trial planned to assess the effect of acupuncture compared with placebo-sham acupuncture and non-acupuncture groups. Therefore, it was designed following the Standards for Reporting Interventions in Clinical Trials of Acupuncture (STRICTA) [24] and reported with the Standard Protocol Items: Recommendations for Interventional Trials (SPIRIT) guidelines [20].

CKD is a debilitating disease, and standards of medical care involve aggressive monitoring for signs of disease progression and early referral to specialists for dialysis or possible renal transplant [36]. As kidney disease progresses, patients often experience a variety of symptoms. The initiation of dialysis can have a variable effect on quality-of-life measures and on the alleviation of uremic signs and symptoms, such as anorexia, fatigue, cognitive impairment, depressive symptoms, pruritus and sleep disturbance [37].

HRQOL has been widely accepted as a valid marker of treatment outcomes and mortality for patients with chronic diseases [38]. Hemodialysis negatively impacts the HRQOL of patients, affecting their physical, functional, metabolic, social and mental conditions, with a high impact on functional capacity when compared to healthy individuals [39,40,41].

Many pharmacological interventions for people with CKD have known risks of adverse events and, according to the literature, acupuncture is commonly used in symptom management for chronic diseases as well as in palliative care [42]. However, the safety and efficacy of acupuncture for people with CKD remains largely unknown. Considering the aims of our study, we expect that verum acupuncture compared to sham acupuncture and non-acupuncture will improve the functional capacity of hemodialysis patients, as evidenced by an increase in the distance walked on the 6MWT and an increase in scores for quality of life. In addition, we expect an increase in handgrip strength and an improvement in peripheral muscle strength. According to Kim et al. (2016), there was low-quality evidence of the short-term effects of manual acupressure as an adjuvant intervention for fatigue, depression, sleep disturbance and uremic pruritus in patients undergoing regular hemodialysis [19]. Under this assumption, this study protocol was designed to check the effect of acupuncture after treatment and at 12 weeks post-treatment. In this way, we expect that the effect of acupuncture will be maintained in the follow-up period.

Some studies, especially in the pain field, suggest that three treatments per week obtain better results than one treatment per week [43,44]. We also expect to see better results with more intensive interventions compared to less frequent and prolonged interventions.

Following review of the literature and to the best of the authors’ knowledge, there are currently no comparable studies. Therefore, our trial seems to be an innovative study for exploring the effect of acupuncture and the frequency of treatment on improving FC and HRQOL in patients undergoing HD. Furthermore, supported by only a few clinical cases reported (personal data) prior to the design and development of the research project, it is possible to predict efficacy and the advantages of integrating acupuncture treatments into routine hemodialysis as a complementary therapy to conventional treatments.

Despite fulfilling strict methodological criteria, it is possible to identify limitations in our study protocol. First, the sample size; second, the TCM practitioner performing the acupuncture treatment will not be blinded due to the nature of the intervention; third, comorbidities inherent to chronic kidney disease may lead to a high dropout rate during the follow-up period.

## 5. Conclusions

In conclusion, this study protocol provides a standardized procedure for conducting our randomized clinical trial. Despite its limitations, we expect the results to provide evidence for the efficacy of acupuncture on FC and HRQOL, as well as for further research to validate the therapeutic effects of acupuncture in patients undergoing HD.

## Figures and Tables

**Figure 1 healthcare-10-02050-f001:**
[figure not shown]
Trial Flow Chart.

**Figure 2 healthcare-10-02050-f002:**
[figure not shown]
Timing of visits and data collection.

**Table 1 healthcare-10-02050-t001:** Details of acupuncture treatment.

Item	Detail	
1. Acupuncture Rationale	(1a) Style of acupuncture	Manual acupuncture.
	(1b) Reasoning for treatment provided, based on historical context, literature sources, and/or consensus methods, with references where appropriate.	The protocol treatment provided is based on traditional meridian theory, literature sources, clinical experience and consensus method of experts in Traditional Chinese Medicine, Acupuncture and Nephrology [25,26,27], members of research team.
	(1c) Extent to which treatment was varied	Experimental (verum acupuncture) group will receive a total of 9 acupuncture treatments, however, will be divided into subgroups A and B. Experimental subgroup A will receive three acupuncture sessions per week over 3 weeks and subgroup B will receive one a week for 9 weeks. The same choice of acupuncture points will be applied to both experimental subgroups A and B.
2. Details of Needling	(2a) Number of needle insertions per subject per session	A total of 5 fixed acupoints and a total of 8 needle insertions per subject and per session.
	(2b) Names of points used	*Taixi* (KI3), bilateral; *Sanyinjiao* (SP6), bilateral; *Zusanli* (ST36), bilateral; *Shenmen* (HT7) unilateral, in the arm without arteriovenous fistula; *Guanyuan* (CV4), unilateral. Acupuncture points will be found according to the WHO points location method.
	(2c) Depth of insertion, based on a specified unit of measurement, or on a particular tissue level	After local area disinfection with alcohol wipes, acupoints CV4, ST36, KI3 and SP6 will be inserted perpendicularly (15 to 20 mm depth) and HT7 inserted slightly obliquely (10 mm depth).
	(2d) Response sought	*De qi* sensation (described as a compositional sensation including numbness, soreness, distention, heaviness) will be achieved through lifting, thrusting and twirling manipulations.
	(2e) Needle stimulation	Manual stimulation. After generating a needling sensation, needles will be manipulated for one minute every ten minutes during needle retention.
	(2f) Needle retention time	25 min.
	(2g) Needle type	Sterilized stainless-steel needle (0.25 × 25 mm) Tewa, asia-med GmbH, [name].
3. Treatment Regimen	(3a) Number of treatment sessions	A total of 9 treatment sessions for both groups.
	(3b) Frequency and duration of treatment sessions	Verum Acupuncture Subgroup A: three times a week for 3 weeks. Verum Acupuncture Subgroup B: once a week for 9 weeks.
4. Other Components of Treatment	(4a) Details of other interventions administered to the acupuncture group	Apart from the usual care routine for hemodialysis sessions, during the study period, no further intervention will be allowed.
	(4b) Setting and context of treatment, including instructions to practitioners, and information and explanations to patients	Treatment sessions will take place at the Hemodialysis Center of TECSAM Tecnologia e Serviços Médicos, SA, in Mirandela, during hemodialysis sessions. Participants will be informed about the entire procedure and a clarification meeting will also be held with the hemodialysis clinical team before treatments starts.
5. Practitioner Background	(5) Description of participating acupuncturists	[name] is a licensed specialist in Traditional Chinese Medicine with professional card number [name] issued by the Regulator of Health System Central Administration in Portugal, ACSS (Administração Central do Sistema de Saúde, I.P.); five years of professional experience; a Traditional Chinese Medicine Master’s degree from Instituto de Ciências Biomédicas Abel Salazar, Universidade do Porto, Portugal; completion of Advanced Chinese Medicine Course from Guangzhou University of Chinese Medicine, Guangzhou, P.R. China.
6. Control or Comparator Interventions	(6a) Rationale for the control or comparator in the context of the research question, with sources that justify this choice	Participants will randomly be assigned to experimental group (verum acupuncture), placebo group (sham acupuncture) or control group (waiting list).
	(6b) Precise description of the control or comparator. If sham acupuncture or any other type of acupuncture-like control is used, provide details as for Items 1 to 3 above.	The placebo group (sham acupuncture) will receive a total of 9 acupuncture treatments, however, will be divided into subgroups A and B. Placebo subgroup A will receive three acupuncture sessions per week over 3 weeks and subgroup B will receive one a week for 9 weeks. Manual acupuncture will be performed as superficial needling (5 mm depth) at non-acupuncture points without an attempt to achieve a *De qi* sensation and without stimulation, lasting 25 min, using a sterilized stainless-steel needle (0.25 × 25 mm; Tewa, asia-med GmbH, [name]).The control group (waiting list) will not receive any acupuncture treatment during the study period. **List of Non-Acupuncture points used and their location** In the present study, the non-acupuncture points selected will be the points located on the non-meridian but near the acupuncture points described above. Non-Acupuncture point 1 (NA1) Located near KI3 (*Taixi*). On the posteromedial aspect of the ankle, at the midpoint of KI3 (*Taixi*) and (*Fuliu*). KI7 (*Fuliu*) is located on the posteromedial aspect of the leg, anterior to the calcaneal tendon, 2 *cun* superior to the prominence of the medial malleolus. Non-Acupuncture point 2 (NA2) Located near SP6 (*Sanyinjiao*). On the leg, at the midpoint of the medial side of the tibia, 1 *cun* distal from SP6 (*Sanyinjiao*). Non-Acupuncture point 3 (NA3) Located near ST36 (*Zusanli*). On the anterior aspect of the leg, at midpoint of ST37 (*Shangjuxu*) and the Gallbladder Meridian. ST37 (*Shangjuxu*) is located on the anterior aspect of the leg, on the line connecting ST35 with ST41, 6 *cun* inferior to ST35, on the tibialis anterior muscle. Non-Acupuncture point 4 (NA4) Located near HT7 (*Shenmen*). On the wrist, at the transverse crease of the wrist, at the midpoint of HT7 (*Shenmen*) and PC7 (Daling), between the Pericardium Meridian and the Heart Meridian. Non-Acupuncture point 5 (NA5) Located near CV4 (*Guanyuan*). On the lower abdomen, 1 *cun* lateral from CV6 (*Qihai*). CV6 (*Qihai*) is located 1.5 *cun* inferior to the center of the umbilicus, on the anterior median line.

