### 2.6. Intervention

The experimental (verum acupuncture) and placebo (sham acupuncture) groups will receive 9 acupuncture treatments. Both groups will be divided into two subgroups with a different treatment frequency: subgroup A will receive 3 acupuncture sessions per week over 3 weeks; and subgroup B will receive 1 acupuncture session per week over 9 weeks. The same selection of acupuncture points, identified according to the method of point location issued by the WHO [23], will be applied to both experimental subgroups A and B. Placebo subgroups A and B will receive acupuncture at the same non-specific acupuncture points. Details of the acupuncture intervention will be described according to the revised Standards for Reporting Interventions in Clinical Trials of Acupuncture (STRICTA) 2010 Checklist [24], as listed in Table 1.

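### Sham point NA1 is defined between two Kidney-channel points, which on its face breaks the protocol's own off-meridian rule for sham points

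*Protocol article*

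**What the plan says.** Table 1, item 6b of the protocol article describes the sham as shallow needling at five sites, NA1 to NA5, and states one criterion for all of them: "the non-acupuncture points selected will be the points located on the non-meridian but near the acupuncture points described above".

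NA1 is the site paired with KI3. Its location is given as "On the posteromedial aspect of the ankle, at the midpoint of KI3 (*Taixi*) and (*Fuliu". The channel code is missing before the second name, but the following sentence supplies it: "KI7 (*Fuliu*) is located on the posteromedial aspect of the leg, anterior to the calcaneal tendon".

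Two other sites are set out differently. NA3 lies "at midpoint of ST37 (*Shangjuxu*) and the Gallbladder Meridian". NA4 lies "at the midpoint of HT7 (*Shenmen*) and PC7 (Daling), between the Pericardium Meridian and the Heart Meridian".

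Item 2b lists KI3 among the verum points, needled on both sides. Item 1b names meridian theory as one of the foundations of the treatment. Objective 2, in the Introduction, is the specific effect of acupuncture relative to placebo.

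**The concern.** The criterion for a sham site is that it is off the meridians. A midpoint between two points of one channel reads most naturally as a site along that channel. NA1 is described in that way, and one of its two landmarks is a point that the verum group has needled.

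The comparison at stake is verum against sham, the only one that addresses objective 2. If a location on a channel matters, as meridian theory holds, NA1 cannot be assumed inert. Activity at a sham site would make the sham group look more like the verum group, so the bias would run toward no difference.

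**Working it through.** The plan gives no figure on this point, so the check sets the texts side by side and counts the scope.

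**Step 1. Each sham definition against the rule (Table 1, item 6b).**

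| Sham site | Paired verum point | Landmarks given | Channels of the landmarks |
|---|---|---|---|
| NA1 | KI3 | midpoint of KI3 and Fuliu (KI7) | Kidney and Kidney |
| NA2 | SP6 | medial tibia, 1 cun below SP6 | offset from one SP point; no second channel named |
| NA3 | ST36 | midpoint of ST37 and the Gallbladder meridian | Stomach and Gallbladder |
| NA4 | HT7 | midpoint of HT7 and PC7 | Heart and Pericardium |
| NA5 | CV4 | 1 cun to the side of CV6 | sideways offset from one CV point |

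NA1 is the only site defined between two points of a single channel. NA3 and NA4 use two different channels, and NA4 is expressly said to lie between them. The text does not show that NA2 or NA5 breaks the rule.

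**Step 2. What follows for NA1.** Both landmarks carry the code KI. That the midpoint lies on the channel is inferred from the shared code; the article does not describe the channel's course between the two points. What the text does establish is narrower: nothing in NA1's definition moves it off the Kidney channel, whereas the definitions of NA3 and NA4 do set those sites between channels.

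**Step 3. Scope.**

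- Sites: 1 of 5 = 20%.
- Verum insertions per session (items 2a and 2b): KI3 × 2 + SP6 × 2 + ST36 × 2 + HT7 × 1 + CV4 × 1 = 8, which reproduces the stated total.
- Sham insertions at NA1: the article gives no sham count. Assuming that sham mirrors verum, 2 of 8 = 25%. If NA1 is needled on one side only, it is 1 insertion.
- Exposure: the definition applies to the whole sham group, planned as at least 24 patients (section 3.4), over nine sessions each: 24 × 9 = 216 planned sessions.

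These are shares of needling, not measures of bias. The documents give no effect per site, so the amount of dilution cannot be computed.

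**Step 4. What still separates sham from verum at this site.** Depth is 5 mm for sham against 15 to 20 mm at KI3 for verum (items 6b and 2c). Sham does not seek De qi and uses no stimulation; verum does both (items 2d and 2e).

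**The case against.** The strongest reply is that the on-channel location is not shown. KI3 and KI7 are not consecutive labels, and a midpoint lies on the channel only if the channel runs directly between them. Settling that needs the point-location standard that the protocol cites, which is not in the documents. The missing code before Fuliu also leaves room for a drafting slip. This stands as a limit on certainty, but it does not remove the conflict: as written, the definition does not support the statement that NA1 is off-meridian, and if there is a slip, the landmark needs correcting anyway.

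It is also fair to say that item 1b lists literature, clinical experience and expert consensus beside meridian theory, and does not claim that shallow, unstimulated needling on a channel has an effect. That stands too, and it is why the bias is conditional.

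A reader might infer more in three respects, and the documents do not support it:

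- **That the sham as a whole is active, so that a null verum-sham result could not be interpreted.** Four of the five sites are not shown to break the rule, depth, De qi and stimulation still differ at every site, and the waiting-list group gives a further reference.
- **That sham needle count, side and fistula arm differ from verum.** Item 2b places HT7 as "Shenmen* (HT7) unilateral, in the arm without arteriovenous fistula", and NA4 carries no such words. That is silence in a condensed article, not a stated difference; each sham site is tied to a listed verum point, so mirroring is a natural reading.
- **That section 2.6 contradicts Table 1.** Its sentence, "Placebo subgroups A and B will receive acupuncture at the same non-specific acupuncture points", is loose wording. The abstract and item 6b both speak of non-acupuncture points, and item 6b lists the sites.

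**Conclusion.** The point holds in a limited form. Followed as written, NA1 does not on its face meet the protocol's own criterion for a sham site, in the group on which objective 2 depends. It concerns 1 of 5 sham sites, or 2 of 8 insertions if sham mirrors verum.

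The conclusion rests on two assumptions: that a midpoint of two points on one channel is at or near that channel, and that location on a channel matters, as meridian theory holds. If both are true, the bias is toward no difference between verum and sham, by an amount that the documents do not allow one to derive. A null result would then be harder to interpret, but not without meaning.

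**What to change.** Before treatment starts, do one of two things in Table 1, item 6b:

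1. Reconcile the NA1 landmark with the off-meridian rule, so that all five sham sites meet the same criterion, and supply the missing channel code. The choice of site belongs to the investigators.
2. If NA1 is kept, withdraw the statement that every sham site is off-meridian, and state with the verum-sham conclusion that one of the five sites is defined by two Kidney-channel points, one of them a verum point.

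Either is a change of wording. Neither needs more patients, staff or time.
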